### Participants

The recruitment of volunteer participants is carried out through the outpatient clinic of the Parisian geriatric hospital (Broca Hospital, Assistance Publique–Hôpitaux de Paris) and its network of professionals, “seniors” associations, and town halls in the Paris region. The inclusion and exclusion criteria for participation in the study are described in Textbox 1.

Information leaflets are given to professionals working in the outpatient hospital of Broca Hospital to distribute them to potential volunteers during consultations. Senior citizens’ associations also distribute the information leaflet to their members and the local city halls disseminate a communication about the study to their users. When OAs wish to volunteer to take part in the trial, they contact the researcher in charge of the study to discuss the modalities in more detail, either by email or by telephone, using the information given on the information leaflet. During this first contact, a detailed explanation of the study is given. After having obtained answers to all their questions, volunteers receive an email with an information note describing the whole study at least 24 hours before inclusion, to give them time to withdraw from participation if wished. Participants are divided into 6 groups of 10 people; 10 robots were available simultaneously. A group of 10 participants was formed every 12 weeks. Each participant who agrees to participate is invited to sign the study’s no-opposition form. The recruitment procedure is described in Figure 1.

Inclusion and exclusion criteria for the DOMIROB study.
**Inclusion criteria**
Being 65 years of age and over;living in the Paris region (Île-de-France);express nonopposition to participating in the study;agree to host a telepresence robot in the home for 12 weeks; andhaving an internet connection at home.
**Exclusion criteria**
Being under 65 years of age;expressed opposition to participating in the study;having moderate or major neurocognitive disorders (Mini-Mental State Examination score <20; [71]);being under guardianship or curatorship; andliving in housing unsuitable for the telepresence robot (surface area and configuration of the home not suitable for robot circulation).

**Figure 1 figure1:**
[figure not shown]
Flow chart of the recruitment process.

### Ethics Approval and Consent

The research protocol was submitted to, and approved by, a French national institutional review board for research involving human participants (Comité de Protection des Personnes, France) on April 27, 2020 (national number: 2020-A00381-38. Trial registration: ClinicalTrials.gov, trial registration number NCT04767100).

### Materials

The TR used in this study is the Cutii, a robotic platform for remote communication. This TR is equipped with a touch screen, microphones, loudspeakers, cameras, an obstacle detector, and a mobile system allowing navigation in the environment (Figure 2). Cutii allows users to maintain a connection with their environment. Its interface has different functionalities allowing, for example, to make video calls and to participate in intellectual (eg, virtual museum tour) and physical (eg, yoga) stimulation activities. Cutii’s services include the following:

An agenda with a calendar to schedule the activities.A contact directory for video calls.An “activities” tab allowing users to participate in collective live sessions of intellectual and physical activities/workshops (eg, gymnastics, yoga, art therapy, virtual museum tours) led by professionals through the video call feature.A “leisure” tab allowing users to play digital games (eg, memory games, sudoku, quiz).A “video” tab to watch documentaries (eg, cooking, traveling, animals’ life).A “teleconsultation” tab that allows users to consult a health professional remotely through the video calling system.

**Figure 2 figure2:**
[figure not shown]
Front and back view of the telepresence robot Cutii. Note: 1: video call camera; 2: touch screen; 3: speaker; 4: microphone; 5: battery indicator light; 6: navigation camera; 7: obstacle detector; 8: power switch; 9: port for dock charging; 10: port for charging by charger.

### Measures

We will use a multimethod approach assessment protocol partly inspired by the MARTA model [43], which has been developed to assess TR interventions involving OAs and complemented by the EUnetHTA model. The assessment uses standardized scales and a semistructured interview format (Multimedia Appendix 1). Sociodemographic data of the participants are also collected (age, sociocultural level, lives alone or accompanied, has children/grandchildren or not) as well as their Mini-Mental State Examination (MMSE) [72] score, which measures the global cognitive functioning, and the 12-Item Short-Form Health Survey (SF-12) [73] score, which measures the perception of one’s health status.

### Standardized Scales

The MMSE [72] measures the global cognitive functioning of OAs. MMSE scores range from 0 to 30, with scores of 26 or higher being considered normal (ie, absence of cognitive impairment). Moderate or major neurocognitive disorders are considered to be present when the score is below 20 [66].

The UCLA (version 3) [65] measures the feeling of loneliness in participants with 20 questions. Participants answer the questions using a Likert scale consisting of 4 response choices: “1=never,” “2=rarely,”, “3=sometimes,” and “4=always.” The scoring of this scale is based on the sum of the scores obtained for each item. The score correlates directly with loneliness, that is, the higher the score, the more lonely the participant feels.

The MSPSS [66] measures the social support perceived by a person. This 12-item scale is divided into 3 subscales: “family,” “friends,” and “others.” Participants respond to each statement using a Likert scale ranging from “1=totally disagree” to “7=totally agree.” The global score allows the researcher to identify 3 levels of perceived social support: high (61-84), moderate (36-60), and low (0-35).

The 30-item GDS [69] measures depressive states in a geriatric population. It is composed of 30 items to which participants answer “yes” or “no.” The total score is calculated by assigning a “0” or a “1” to each item according to the participant’s response. The highest score is therefore 30. A score ranging from 0 to 9 represents a normal state. A score from 10 to 19 or from 20 to 30 represents, respectively, a moderate or severe depression.

The SF*-*12 [73] is a questionnaire developed from the SF-36 questionnaire. The SF-12 provides a self-reported measure of the impact of physical and mental health in the everyday life of individuals. The average score is 50 and all scores above this threshold are considered normal.

The SUS [67] defines the level of usability of a system, tool, software, or digital technology with regard to its effectiveness, efficiency, and overall ease of use. After having experienced the use of the device, the person responds to 10 items using a Likert scale consisting of 5 responses ranging from “1=strongly disagree” to “5=strongly agree.” The total score ranging from 0 to 100 represents a gradually increasing usability. A product is considered as having a good usability if the score is above 70.

The ALMERE model [68] measures OAs’ acceptance toward socially assistive robots. It can be used to predict and understand the use of a system by observing the influences on the intention to use it. The ALMERE model questionnaire is composed of 39 items divided into 13 dimensions: “Anxiety,” “Attitude Towards Technology,” “Facilitating Conditions,” “Intention to Use,” “Perceived Adaptiveness,” “Perceived Enjoyment,” “Perceived Ease of Use,” “Perceived Sociability,” “Perceived Usefulness,” “Social Influence,” “Social Presence,” “Trust,” and “Use.” These dimensions predict the actual intention to use the system. To answer the items, the participants respond using a 5-point Likert scale ranging from “1=strongly disagree” to “5=strongly agree.” Scores of 1 and 2 represent poor satisfaction, 3 denotes fair satisfaction, 4 means good satisfaction, and 5 promotes excellent satisfaction.

The PIADS [70] is a self-report questionnaire designed to assess the effects of an assistive device on functional independence, well-being, and quality of life. Participants respond to 26 items on a 7-point Likert scale ranging from “–3” to “+3.” The final score of –3 represents the strongest negative impact, 0 indicates no perceived impact, and 3 denotes the strongest positive impact.

Measurements performed during the experimental phase of the DOMIROB study are listed in Table 1. The calendar of the assessments is specified in Table 2.

**Table 1 table1:** DOMIROB project protocol measures.

Measurement tools	Dimensions assessed
Mini-Mental State Examination (MMSE) [72]	Global cognitive efficiency
Perceived Loneliness Scale (UCLA) [65]	Subjective feelings of loneliness
Multidimensional Scale of Perceived Social Support (MSPSS) [66]	Perceived social support (social isolation)
Depression: Geriatric Depression Scale (GDS) [69]	Depressive states
Perceived health status: 12-item Short Form Health Survey (SF-12) [73]	Self-assessment of health
System Usability Scale (SUS) [67]	Telepresence robot usability
Acceptance model (ALMERE) [68]	Telepresence robot acceptance
Psychological Impact of the Assisted Device (PIADS) [70]	Psychosocial impact of a device
Sociodemographic data	Age, socioeducational level, and family status
Semistructured interview	Eight dimensions of the European Network for Health Technology Assessment Core Model: “Health Problem and Current Use of the Technology,” “Description and Technical Characteristics of the Technology,” “Safety,” “Clinical Effectiveness,” “Costs and Economic Evaluation,” “Ethical Analysis,” “Organizational Aspects,” “Patients and Social Aspects” [65]

**Table 2 table2:** Semistructured interview based on the European Network for Health Technology Assessment Model.

Item	Health Technology Assessment dimension
What impact did the robot have on your health/well-being?	Current Use of the Technology (CUR)
How did you find the robot’s features and services? Did you find them useful? Why do you think so?	Description and Technical Characteristics of the Technology (TEC)
What do you think are the potential risks and side effects caused by the use of the robot? What can be done to prevent them?	Safety (SAF)
Do you think this robot can have an impact on the loneliness/isolation of the users? Why?	Clinical Effectiveness (EFF)
How much would you be willing to invest to benefit from the robot in your home? Would you prefer to purchase or to rent the robot? In the case of a rent, would it be for a short or long term?	Costs and Economic Evaluation (ECO)
In your opinion, what are the ethical issues to be identified and defined before the deployment of these robots in the homes of future users?	Ethical Analysis (ETH)
In your opinion, what skills and knowledge are necessary for a good deployment of these robots in users’ homes?	Organizational Aspects (ORG)
What factors would restrain you from using this type of robot?	Patients and Social Aspects (SOC)
Nonapplicable	Legal Aspects (LEG)

### Semistructured Interview

We designed a semistructured interview based on the EUnetHTA Core Model version 3.0 [65]. This model allows a systematic assessment of the characteristics, effects, or impacts of health care technologies. The main objective of the HTA model is to facilitate decision making in the field of health care to improve the uptake of new health technologies.

The 9 dimensions of the EUnetHTA Core Model allow the identification of issues that are necessary for the deployment and use of new technological tools in the field of health. These dimensions include “Health and Current Use of the Technology,” “Description and Technical Characteristics of the Technology,” “Safety,” “Clinical Effectiveness,” “Costs and Economic Evaluation,” “Ethical Analysis,” “Organizational Aspects,” “Patients and Social Aspects,” and “Legal Aspects.” The interview guide used in the DOMIROB protocol was designed using the first 8 dimensions of the EUnetHTA Core Model (Table 2). The “Legal” dimension was excluded because its assessment did not directly concern the TR end users and was therefore entrusted to a specialized consulting firm. The semistructured interviews were integrated to our protocol with the aim of examining different dimensions that may inform the choice of TRs to provide social and care services to OAs and to establish recommendations for the use of TRs for future users.

### Procedure and Time Schedule

All stages of the experimental phase are illustrated in Figure 3, which describes the different actors involved in each step of the experimental phase, its length, the eventual assessment carried out at that moment, and the respective assessment tools.

During their participation in the protocol, the participants complete 4 assessments (including scales and interviews) as shown in Table 3.

The first evaluation is performed at the time of inclusion at week 0 (ie, approximately 1 week before the implementation of the TR in the volunteers’ homes; Figure 4). A second evaluation (intermediate evaluation) is conducted 6 weeks after the beginning of the experiment at home. A third evaluation (final evaluation) is carried out at the end of the implementation phase (week 12). To conclude the participation in the protocol, the volunteers are invited to take part in a final assessment (follow-up evaluation) at week 24, approximately 12 weeks after the robot has been removed from the participants’ homes. Assessments of participants are conducted face-to-face for the inclusion, and then via the video call functionality of the Cutii robot or by telephone at weeks 6, 12, and 24. Semistructured interviews at week 12 are conducted by a psychologist and recorded using a voice recorder to be transcribed and analyzed.

**Figure 3 figure3:**
[figure not shown]
Steps of the experimental phase. GDS: Geriatric Depression Scale; MMSE: Mini-Mental State Examination; MSPSS: Multidimensional Scale of Perceived Social Support; PIADS: Psychosocial Impact of Assistive Devices Scale; SF-12: 12-Item Short-Form Health Survey; SUS: System Usability Scale; UCLA: Perceived Loneliness Scale.

**Table 3 table3:** Calendar of the assessment carried out in the DOMIROB protocol.

Measures	Evaluations			
	Inclusion (week 0)	Week 6	Week 12	Week 24
Mini-Mental State Examination (MMSE)	✓			
Perceived Loneliness Scale (UCLA)	✓	✓	✓	✓
Multidimensional Scale of Perceived Social Support (MSPSS)	✓	✓	✓	✓
Geriatric Depression Scale (GDS)	✓	✓	✓	✓
12-Item Short-Form Health Survey (SF-12)	✓			
System Usability Scale (SUS)		✓	✓	
The ALMERE model		✓	✓	
Psychosocial Impact of Assistive Devices Scale (PIADS)		✓	✓	
Sociodemographic data	✓			
Semistructured interview (Health Technology Assessment model)			✓	

**Figure 4 figure4:**
[figure not shown]
Experimental and evaluation phases in the DOMIROB protocol.

### Installation and Training

For the implementation phase of the robot, a team of 2 professionals, experts of the Cutii robot, install the robot in the participant’s home. The team and the participant choose the location of the dock of the robot, which is close to an outlet to facilitate its recharging. During the intervention, the team connects the robot to the participant’s Wi-Fi network and ensures it works properly. After the installation, the team provides the participants with a 60-minute training session to familiarize them with its functionalities and operation. The training session includes information about how to use the robot, its maintenance, and the procedure to follow in case of malfunction. In case of malfunction, participants can contact the project support team at any time during the study. Participants are informed that their environment can be visualized during the video call service and the group workshops so that they can make the arrangements when necessary to preserve their privacy.

### Period of Use of the Robot

During the experimental phase, participants are invited to discover the different functionalities of the robot. Participants are free to use the TR as needed and wished. Volunteers can discover the “video call” functionality by making videoconferences with their relatives or taking part in the live sessions (workshops, activities). Every week the workshop facilitators offer live cultural and physical workshops (eg, yoga, soft gym, guided tours of museums) through the robot’s “video call” feature. The robot also offers users games, reading, and music applications.

### Data Analysis

#### Quantitative Analysis (Standardized Scales)

The descriptive data for all the questionnaires will be presented in the form of both average scores and SDs. Inferential statistical analyses of the results obtained during the different evaluation weeks will then be performed. All collected data will be analyzed using the open-source statistics program Jeffreys’s Amazing Statistics Program (version 0.14.1; JASP Team). For the scores of questionnaires on social isolation (GDS, MSPSS, and UCLA), a 1-way ANOVA or its nonparametric alternative (the Friedman test) will be applied according to the result of Shapiro-Wilk normality test. Then the Mauchly test of sphericity will be performed to see if any postcorrection of the degrees of freedom has to be made so that the valid *F*-ratio can be obtained. For the questionnaires concerning the use of TRs (SUS, PIADS, and ALMERE), the Shapiro-Wilk test will be used to verify the assumption of normal distribution of data to determine whether the paired (2-tailed) sample *t* test or Wilcoxon signed-rank test will be used. It should be noted that for a better interpretation of the results of the ALMERE, the Cronbach α index will be used to ensure a proper internal consistency of the questionnaire. Similarly, the multiple linear regression will be used to determine the predictive links between different aspects presented in the ALMERE model.

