### Determination of Sample Size

The sample size and power calculation for this study were performed based on 1 of the main outcome measures for this study: the feeling of loneliness, as assessed with the Perceived Loneliness Scale (UCLA; version 3) [65]. From a statistical point of view, we consider that the average score for the UCLA scale, observed for people aged 65 years and over, is 31.51/80 [65]. The higher the score, the greater the perceived loneliness is evaluated. Therefore, our hypothesis aims at a decrease in the average score in the UCLA scale of 3-5 points. If we want to show a decrease of 15% in the average score on the UCLA, between the assessment done at week 0 and week 24 with a power of 0.8 and a risk α of .05, then 60 individuals should be included. A decrease in the UCLA loneliness score of 15% after a 12-week implementation of the TR is clinically relevant.

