### Objectives

#### Main Objective and Primary Outcome Measures

The main objective of this study is to measure the impact of a 12-week intervention using a TR in the home of OAs on their feeling of loneliness and social isolation. To measure the impact of TRs on the feeling of loneliness, we will use the UCLA (version 3) [65]. We will assess social isolation using the Multidimensional Scale of Perceived Social Support (MSPSS), which is a tool for measuring the perception of social support that a person has [66]. We will compare the results obtained in the assessments performed at weeks 0, 6, 12, and 24 to identify the possible decreases in the scores of the different scales at different times of the implementation of the TR at home.

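### The study is sized for one UCLA contrast (week 0 to week 24), but the only named UCLA test is a four-visit omnibus ANOVA or Friedman test chosen by Shapiro-Wilk

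*Protocol article*

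**What the plan says.** The Determination of Sample Size section defines the target as "a decrease of 15% in the average score on the UCLA, between the assessment done at week 0 and week 24". The stated power is 80% at a 5% alpha, and the resulting sample is 60 people. It takes as its starting value that "the average score for the UCLA scale, observed for people aged 65 years and over, is 31.51/80". The last sentence of the same section calls a 15% fall after the 12-week implementation clinically relevant, so the section refers to two time points.

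The Main Objective and Primary Outcome Measures section is broader: "We will compare the results obtained in the assessments performed at weeks 0, 6, 12, and 24", with the purpose of identifying possible decreases at different times.

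The Quantitative Analysis section then gives one inferential procedure for UCLA, MSPSS and GDS: "a 1-way ANOVA or its nonparametric alternative (the Friedman test) will be applied according to the result of Shapiro-Wilk normality test". It continues: "Then the Mauchly test of sphericity will be performed to see if any postcorrection of the degrees of freedom has to be made". The sphericity check and the Friedman alternative show that the ANOVA is a repeated-measures one. No contrast, primary time point or interval for the change is named. The section also promises descriptive results: "The descriptive data for all the questionnaires will be presented in the form of both average scores and SDs".

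**The concern.** A four-visit omnibus test and a two-visit contrast are different hypotheses. The omnibus null is that all four visit means (or, for Friedman, rank distributions) are equal, and it can be rejected because of any visit and in either direction. The sample-size target is a fall between two named visits. A significant omnibus result is therefore compatible with no change from week 0 to week 24, and the stated 80% power belongs to a test that the analysis section does not name.

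The Shapiro-Wilk switch adds a second difficulty. Which test is run, and so whether the result concerns means or ranks, is settled after seeing the data. The trial has no control group, so the within-person change is its only effect estimate. It matters that this estimate is defined in advance and has an interval.

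**Working it through.** **Inputs from the protocol.** Mean UCLA 31.51; fall 15%; n = 60; power 0.80; alpha .05; visits at weeks 0, 6, 12 and 24; UCLA has 20 items scored 1 to 4, so its range is 20 to 80. The SD of the change, the within-person correlation and the sidedness are not given.

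**1. The plan's own figure.** The target fall is 0.15 × 31.51 = 4.73 points. With no SD of change stated, 60 cannot be reproduced, only inverted. The paired normal formula is n = (SD × (z_alpha + z_power) / delta)². Two-sided, SD = 4.7265 × √60 / (1.960 + 0.842) = 13.07, a standardised change of 0.362. One-sided, the SD is 14.72. With the t distribution in place of the normal, the standardised change giving 80% is 0.368, that is, an SD of 4.7265 / 0.368 = 12.8.

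**2. Omnibus power at that effect size.** Let d be the fall whose standardised size is 0.368. Under compound symmetry the within-person error variance is half the variance of a change. The noncentrality is therefore λ = n × 2 × 0.368² × SS = 16.25 × SS, where SS is the sum of squared deviations of the four visit means (in units of d) from their average. Power is the upper tail of a noncentral F(3, 177) beyond its 5% critical value.

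| Visit means at weeks 0, 6, 12, 24 | SS | λ | Omnibus power | True week 0 to 24 change |
|---|---|---|---|---|
| 0, -d/2, -d, 0 | 0.6875 | 11.17 | 0.80 | none |
| 0, 0, -d, 0 | 0.75 | 12.19 | 0.84 | none |
| 0, -d, -d, 0 | 1.00 | 16.25 | 0.93 | none |
| 0, -d/4, -d/2, -d | 0.547 | 8.89 | 0.69 | d |
| 0, -d/2, -d, -d | 0.6875 | 11.17 | 0.80 | d |
| 0, -d, -d, -d | 0.75 | 12.19 | 0.84 | d |

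The first three rows show a test that is usually significant when the powered contrast is zero. The fourth shows a shortfall against 80% for a decline spread over the visits. The last two show none for a sustained effect. SS does not change if all signs are reversed, so a rise in loneliness is detected as readily as a fall.

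**3. Simulation check.** This used 3000 trials per cell, n = 60, compound symmetry with correlation 0.5 or 0.7, normal scores and an SD of change of 13.07. For 0, -d/2, -d, 0 the Greenhouse-Geisser ANOVA was significant in 76-77% of trials, Friedman in 65-66%, and the paired week 0 to 24 test in 5%. For effects fully present at week 24 the ANOVA had 0.78-0.83, Friedman 0.65-0.71 and the paired test 0.78-0.79. The Friedman figures are for normal scores and are only indicative for skewed ones.

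**4. How often the switch leads to Friedman.** The assumed mean is 31.51 - 20 = 11.51 points above the floor. Scores were simulated from a skewed distribution bounded at 20 and 80, with an assumed SD of 6 to 12 and correlation 0.7.
- Shapiro-Wilk rejected at a given visit in 68-100% of trials.
- It rejected at one or more of four visits in 96-100%.
- Applied to pooled ANOVA residuals, it rejected in 34-99%.
- With truly normal scores checked at each visit, it still rejected at least once in 18%.

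The protocol does not say which quantity is tested.

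**5. Complete cases.** In their classical form both named tests use only people with all four visits. Suppose independent missingness of 3%, 5% or 10% at each post-baseline visit (assumed). Then 60 × 0.97³ = 55, 60 × 0.95³ = 51 or 60 × 0.90³ = 44 people have all four visits, against 58, 57 or 54 with weeks 0 and 24.

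**The case against.** The omnibus test fits the primary-outcome section, which does call for a comparison across all four visits, and it is an ordinary first step. Post hoc comparisons and missing-data rules are commonly left to a full protocol or analysis plan that is not shown, so their absence from an article is not an error. This stands, and it limits the complete-case remark to a property of the methods named. It does not remove the mismatch: the article itself states one contrast for the sample size and a different hypothesis for the test.

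Four stronger readings are tempting but not supported:
- **That the omnibus ANOVA generally loses power.** It does not for a sustained effect. For 0, -d/2, -d, -d/2 its power is 0.65, but the week 0 to 24 change there is only d/2 and the paired test has 29%, so on the stated contrast the omnibus does better.
- **That the analysis will give no mean change.** Means and SDs are promised for every questionnaire, so a difference can be read off. What is not planned is an interval.
- **That Friedman is practically certain.** This depends on an unstated score distribution and on whether scores or residuals are tested.
- **That people who return the robot early are excluded, favouring the robot.** The Procedure and Time Schedule section allows telephone assessment at weeks 6, 12 and 24, and nowhere says that anyone is dropped.

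**Conclusion.** The point holds as a mismatch between two stated rules. The sample size rests on the UCLA change from week 0 to week 24, and the named test does not test that change. The consequence can be large: omnibus power is 0.80 to 0.93 when the true week 0 to 24 change is zero after a transient fall, and 0.69 rather than 0.80 for a decline spread over the visits. These figures assume n = 60, compound symmetry, a two-sided 5% level and the effect size implied by 80% power for the paired contrast. Choosing the method by Shapiro-Wilk is also a poor rule in itself. Arriving at Friedman is plausible for a score with a floor of 20 and an assumed mean of 31.51, but the documents do not establish it. A reader might infer that the primary result is bound to be biased or underpowered; neither follows.

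**What to change.** 1. In Determination of Sample Size, reconcile week 24 with the 12-week wording and name one primary UCLA contrast. If week 12 is chosen, restate the power calculation for it. In either case state the SD of change used.
2. In Quantitative Analysis, estimate that contrast with a 95% confidence interval from a prespecified linear mixed model, with visit as a categorical effect and all observed visits included. Report the other time point as secondary.
3. Remove the Shapiro-Wilk switch for these scales. Handle skewness with a bootstrap or robust interval as a fixed sensitivity analysis.

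The cost is a change of wording and slightly more analysis work, possibly in another package; no new data are needed. The mixed model does not remove bias from informative dropout, and it does not make up for the lack of a control group.
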